## Abstract

**Background:**

Second primary malignancies are a major cause of excess morbidity and mortality in cancer survivors. Hodgkin lymphoma survivors who were treated with infradiaphragmatic radiotherapy and/or high-dose procarbazine have an increased risk to develop colorectal cancer.

Colonoscopy surveillance plays an important role in colorectal cancer prevention by removal of the precursor lesions (adenomas) and early detection of cancer, resulting in improved survival rates. Therefore, Hodgkin lymphoma survivors treated with infradiaphragmatic radiotherapy and/or high-dose procarbazine could benefit from colonoscopy, or other surveillance modalities, which are expected to reduce colorectal cancer incidence and mortality. Current knowledge on clinicopathological and molecular characteristics of therapy-related colorectal cancer is limited. The pathogenesis of such colorectal cancers might be different from the pathogenesis in the general population and therefore these patients might require a different clinical approach.

We designed a study with the primary aim to assess the diagnostic yield of a first surveillance colonoscopy among Hodgkin lymphoma survivors at increased risk of colorectal cancer and to compare these results with different screening modalities in the general population. Secondary aims include assessment of the test characteristics of stool tests and evaluation of burden, acceptance and satisfaction of CRC surveillance through two questionnaires.

**Methods/Design:**

This prospective multicenter cohort study will include Hodgkin lymphoma survivors who survived ≥8 years after treatment with infradiaphragmatic radiotherapy and/or procarbazine (planned inclusion of 259 participants). Study procedures will consist of a surveillance colonoscopy with removal of precursor lesions (adenomas) and 6–8 normal colonic tissue biopsies, a fecal immunochemical test and a stool DNA test. All neoplastic lesions encountered will be classified using relevant histomorphological, immunohistochemical and molecular analyses in order to obtain more insight into colorectal carcinogenesis in Hodgkin lymphoma survivors. The Miscan-model will be used for cost-effectiveness analyses.

**Discussion:**

Evaluation of the diagnostic performance, patient acceptance and burden of colorectal cancer surveillance is necessary for future implementation of an individualized colorectal cancer surveillance program for Hodgkin lymphoma survivors. In addition, more insight into treatment-induced colorectal carcinogenesis will provide the first step towards prevention and personalized treatment. This information may be extrapolated to other groups of cancer survivors.

**Trial registration:**

Registered at the Dutch Trial Registry (NTR): NTR4961.

## Background

### Colorectal cancer risk in cancer survivors

Because of the improvements of cancer treatment over recent decades, cancer survival has greatly increased. A major and serious complication of cancer treatment is the occurrence of second primary malignancies, which accounts for approximately 18% of all cancers in the Western world [1, 2]. The development of second primary malignancies is influenced by multiple factors, including genetic predisposition, environmental factors and lifestyle factors. Moreover, certain anticancer treatments have the (paradoxical) capability to cause cancer, due to mutagenic and genome destabilizing effects.

Hodgkin lymphoma (HL) survivors have a substantial excess risk of developing colorectal cancer (CRC) [3–8]. The risk of CRC is also increased in survivors of many other malignancies, including survivors of testicular cancer, Wilms tumor, central nervous system malignancies and bone cancer [6–9]. The excess risk of CRC is strongly related to primary cancer treatment with radiotherapy or alkylating agents [5, 7, 8, 10]. A recent analysis of a Dutch multicenter HL cohort showed an increased incidence of CRC in long-term survivors of HL compared with the general population (SIR 2.4 (95% CI 1.8–3.2). HL survivors who were treated with high dose (>4.2 g/m2) procarbazine, or with infradiaphragmatic radiotherapy in combination with chemotherapy have an even higher risk (SIR 4.3 (95% CI 2.9–6.1) and 5.7 (95% CI 3.7–8.2), respectively) [3, 5].

### Colorectal cancer surveillance

HL survivors have a clearly increased risk of developing CRC for a prolonged period, starting 10 years up to over 30 years after receiving infradiaphragmatic radiotherapy and/or procarbazine [5]. These HL survivors may therefore benefit from a CRC surveillance program. Colonoscopy surveillance is important for CRC prevention in high-risk populations by early detection and removal of the precursor lesions (adenomas) with malignant potential, resulting in improved survival rates [11–13]. Surveillance programs in high-risk groups are different from screening programs in the general population, for which the fecal occult blood test-based program is the method of choice in the European Union [14]. However, the fecal occult blood test is inadequate for high-risk populations because of the relatively low sensitivity for advanced adenomas.

In the Netherlands, surveillance is performed in specific high-risk populations, like those with familial CRC or Lynch syndrome [15]. In current Dutch clinical practice, no colonoscopy surveillance program exists for HL survivors at high risk of CRC, because important requirements for screening/surveillance are not met, i.e. the presence of a recognizable latent stage of disease and knowledge of natural history. The pattern of development of a precursor lesion into cancer has substantial influence on the preventive effects of colonoscopy surveillance, and this pattern is unknown for CRCs that develop in HL survivors. Flat adenomas in the presence of chronic radiation colitis have been described in case reports on cancer survivors [16, 17]. In addition, a recent review reported a high frequency of mucinous adenocarcinomas in case reports on radiotherapy-associated rectal cancer, suggesting a difference in tumor biology as compared with sporadic CRCs [18].

It is thus important to personalize CRC prevention programs for different subgroups.

Because of the high risk of CRC in HL survivors, and the lack of data on the pathogenesis of these cancers, we designed a prospective cohort study that evaluates diagnostic yield and test characteristics of colonoscopy surveillance in HL survivors. These characteristics will also be evaluated for stool tests. In addition, the cost-effectiveness and patient perception of CRC surveillance will be evaluated. This knowledge could lead to a personalized CRC surveillance program for HL survivors.

## Methods

### Objectives

The objective of this study is to provide information on the potential benefit of a personalized CRC surveillance program for HL survivors at increased risk of developing CRC.

The primary aim is to assess the diagnostic yield of advanced colorectal neoplasia detected by colonoscopy among HL survivors at increased risk of CRC. Advanced colorectal neoplasia is defined as an adenoma with high grade dysplasia, ≥25% villous component or ≥10 mm diameter or CRC.

Secondary aims are to assess the test characteristics of stool tests (fecal immunochemical test (FIT), and stool DNA (sDNA test)) and to examine patient perception (burden, acceptance and satisfaction) and cost-effectiveness of CRC surveillance in HL survivors. In addition, the clinicopathological and molecular characteristics of therapy-related colorectal neoplasia will be evaluated.

The Medical Ethics Committee of the Netherlands Cancer Institute approved this study protocol and the study is currently ongoing. We adhered to SPIRIT guidelines.

### Study design

#### Population

This prospective multicenter cohort study will include patients from a large cohort of HL survivors who were treated for HL after 1965. HL treatment data and follow-up data were collected as previously described [3, 5, 19, 20].

Patients who meet the inclusion criteria will be invited for study participation in one of the Dutch study centers (The Netherlands Cancer Institute, Amsterdam, Erasmus MC, University Medical Center, Rotterdam, University Medical Center Utrecht, Utrecht and Radboud University Medical Center, Nijmegen). The inclusion criteria consist of the treatment of primary or recurrent HL consisting of at least one of the following treatments:infradiaphragmatic radiotherapy consisting of at least para-aortic and iliac fieldschemotherapy containing a cumulative procarbazine dose of ≥2.8 g/m^2^
infradiaphragmatic radiotherapy (any field (s)) and chemotherapy (any regimen)

Additional inclusion criteria are HL diagnosis at the age of 16–50 years, survival of at least 8 years after this treatment, current age of 25 years or older and life expectancy of 5 years or more. Patients who meet one of the following criteria will be excluded: proctocolectomy, colonoscopy surveillance for other indications (including hereditary CRC syndrome, familial CRC syndrome, inflammatory bowel disease, colorectal adenoma, history of CRC), colonoscopy in the past 5 years, on-going cytotoxic treatment or radiotherapy for malignant disease, coagulopathy (prothrombin time > 50% of control; partial thromboplastin time > 50 s) or anticoagulants (vitamin K antagonists or new oral anticoagulants) that cannot be stopped, comorbidity leading to an impaired physical performance (World Health Organization performance status 3–4) or mental retardation and no informed consent.

The population of HL survivors in the four participating centers consists of approximately 850 eligible participants. Patients will be invited by their treating physician, either a radiation oncologist or a medical oncologist/hemato-oncologist. When patients are no longer under surveillance, they will be invited to a lymphoma Survivorship Care Clinic to inform them about the risk of late effects of Hodgkin lymphoma treatment and to perform surveillance according to standardized follow-up guidelines [21]. These Survivorship Care Clinics are being set up by a national consortium i.e. the BETER consortium (Better care after HL, Evaluation of long-term Treatment Effects and screening Recommendations). This consortium aims to reduce morbidity and mortality of late adverse effects of HL treatment by a survivorship care program in order to improve life expectancy and quality of life of HL survivors. At the Survivorship Care Clinic, eligible participants will be invited for participation in this CRC surveillance research project.

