### Study procedures

#### Colonoscopy

All patients will receive oral and standard written information about the preparation and the colonoscopy by their treating physician or by the gastroenterologist. The preparation will be performed as for routine colonoscopy by ingesting a commonly prescribed oral electrolyte lavage solution. Standard methods of conscious sedation (midazolam and/or fentanyl citrate or propofol) and cardiopulmonary monitoring will be used during the procedure. The colonoscopy will be performed by experienced gastroenterologists (>1000 colonoscopies and certified for performing colonoscopies in the Dutch population-based CRC screening program). Quality measures of colonoscopy will include registration of location of deepest insertion, withdrawal time, quality of preparation (Boston scale), colonoscopy difficulty (5-point scale), patient discomfort (Gloucester comfort scale) and level of sedation (Leeds score).

In the presence of colorectal neoplasia, polypectomy will be performed or biopsies will be taken according to standard protocol. The following data will be collected concerning colorectal neoplasia: number, morphology (Paris classification), size (measured with an open biopsy forceps), location (cecum, ascending, hepatic flexure, transverse, splenic flexure descending, sigmoid or rectum) and details about the polypectomy.

In the presence of a polyp of ≥10 mm, field biopsies will be taken and a fragment of the polyp will be allocated for study purposes after routine pathological evaluation. Four biopsies of normal mucosa of the transverse colon and two to four biopsies of normal mucosa of the descending colon will be taken (in both patients who did and who did not receive infradiaphragmatic irradiation). The transverse colon is the colonic segment that usually receives the highest dose of irradiation in infradiaphragmatic radiotherapy, whereas the descending colon receives a low dose of irradiation. In case of an additional surgical resection of a neoplastic lesion, part of the resection specimen will be allocated for study purposes. Study material will be stored at the participating hospitals and shipped to the Netherlands Cancer Institute for analyses.

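### The prothrombin limit in the coagulopathy exclusion is met by a normal result, so it cannot identify impaired clotting

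*Protocol article*

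**What the plan says.** The exclusion list in the protocol article (Methods, Study design, Population) opens with "Patients who meet one of the following criteria will be excluded". One item is "coagulopathy (prothrombin time > 50% of control; partial thromboplastin time > 50 s", followed in the same item by the alternative "anticoagulants (vitamin K antagonists or new oral anticoagulants) that cannot be stopped". The article mentions prothrombin nowhere else and does not say whether the percentage is a time or an activity.

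Two other places show what the limit is for and how it has been used:

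- **Procedures.** The Colonoscopy section states "In the presence of colorectal neoplasia, polypectomy will be performed or biopsies will be taken according to standard protocol". For all participants it adds "Four biopsies of normal mucosa of the transverse colon and two to four biopsies of normal mucosa of the descending colon will be taken".
- **Eligible pool.** The Population section states "The population of HL survivors in the four participating centers consists of approximately 850 eligible participants".

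**The concern.** An exclusion limit for coagulopathy should be met by patients whose clotting is impaired and not by patients whose clotting is normal. The prothrombin limb does not do this, because a result equal to the control already lies above half the control.

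At stake is a numeric bleeding-safety limit. It applies before any polypectomy and before 4 + 2 = 6 to 4 + 4 = 8 biopsies of normal mucosa. Those biopsies are taken to study the effect of irradiation, so a participant with no lesion undergoes them purely for research. The limit protecting that participant should be one a site can apply and a monitor can check. On this limb the printed text allows neither.

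**Working it through.** No sample-size, power or alpha figure is involved. The check is whether the printed limit separates normal from impaired clotting.

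**Inputs from the article (Population)**

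- Prothrombin limb: more than 50% of control.
- Partial thromboplastin limb, for comparison: "partial thromboplastin time > 50 s".
- Meeting a listed criterion excludes the patient.

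**Assumption not in the article.** A control prothrombin time of 12 s, range 11 to 14 s, used only for illustration. The conclusion needs only that a normal result is about 1.0 × control.

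**Reading 1: clotting time**

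- Printed cut-off = 0.5 × control.
- Cut-off if 50% above control was meant = 1.5 × control.
- Ratio = 1.5 / 0.5 = 3, whatever the control value.

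| Assumed control | Printed cut-off (0.5 ×) | Prolongation cut-off (1.5 ×) |
|---|---|---|
| 11 s | 5.5 s | 16.5 s |
| 12 s | 6 s | 18 s |
| 14 s | 7 s | 21 s |

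A normal result is 1.0 × control. Since 1.0 > 0.5, it meets the printed exclusion; since 1.0 < 1.5, it would not meet the corrected one. With a 12 s control, a normal 12 s result exceeds 6 s but not 18 s. A prolonged time also exceeds 6 s, so the printed limb treats normal and prolonged results alike.

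**Reading 2: activity**

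- Normal is about 100%. Since 100% > 50%, it meets the printed exclusion.
- A reduced activity, for example 30%, is not above 50% and is not caught by this limb.
- With the sign reversed (below 50%), 100% is not excluded and 30% is.

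**Comparison with the other limb.** A partial thromboplastin time above 50 s flags a prolonged time, which is the right direction. Together with the word coagulopathy, this makes the intent clear and confines the error to the prothrombin limb.

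**Which correction was meant.** The time correction needs the limit to be above control, where the text says of control. The activity correction needs the opposite sign and a different quantity from the printed time. Each departs from the text somewhere, and nothing in the article decides between them.

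**The case against.** The strongest reply accepts the arithmetic and disputes the weight. It has four parts.

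- **Intent is obvious.** The item is headed coagulopathy, and no clinician would exclude people because their clotting is normal. This stands as to practice: about 850 survivors are counted as eligible and the study is described as ongoing, so the text is evidently not being applied literally. But clear intent to exclude impaired clotting does not supply the number. Two limits on different scales fit that intent.
- **The article is a condensed text.** The full protocol may carry correct wording. This stands as a limit on the claim: what the sites work from is unknown. It does not excuse the article, which gives a specific limit and gives it wrongly; this is not a detail left out.
- **No harm follows, and other safeguards remain.** On the time reading, a prolonged result still meets the limb, so the slip can only over-exclude; low values pass this limb only on the activity reading. The partial thromboplastin limb, the anticoagulant exclusion and experienced endoscopists also remain. All of this is correct, and no harm to a participant is claimed. However, the anticoagulant item covers only drugs that cannot be stopped, so it does not replace a prothrombin limit for other causes of impaired clotting.
- **The limbs are joined only by a semicolon.** If both had to be met, normal patients would not be excluded. That is a fair point against saying the printed text excludes everyone with normal clotting, and that is not asserted here. It does not rescue the prothrombin limb: on the time reading the limb would then simply add nothing.

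**Conclusion.** The prothrombin limb is wrong as written. A normal result meets it on either scale, so it does not identify impaired clotting. On the time scale the printed limit is one third of the limit for a 50% prolongation (0.5 against 1.5 × control); on the activity scale the sign is reversed. This rests only on a normal result being about 100% of control; the values in seconds are illustrative.

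The consequence is limited. The planned 259 participants, the primary analysis and the partial thromboplastin limb are unaffected, and literal use by sites is unlikely. What fails is the printed limit itself: anyone relying on this text must supply a direction and a unit, and eligibility on this limb cannot be verified from it. For a numeric safety limit ahead of research biopsies, that should be corrected.

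**What to change.** Replace the prothrombin limb with one limit that states its direction and unit:

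- prothrombin time prolonged by more than 50% above control (more than 1.5 × control); or
- if percent activity was meant, prothrombin activity below 50% of control.

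The sponsor's clinical lead should confirm which was intended and issue that single wording to all four centres. Leave the partial thromboplastin limb and the anticoagulant exclusion unchanged.

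The cost is a one-line correction. Included participants need checking against the confirmed limit only if the sites' working protocol turns out to carry the same wording.

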#### Control population

For the diagnostic yield of colonoscopy, FIT and sDNA test, comparison with the asymptomatic Dutch general population will be performed using the data of the COCOS study [22]. In this study primary colonoscopy screening was performed in 1276 asymptomatic individuals out of 5924 randomly selected invitees between 50 and 75 years of age. Advanced neoplasia (defined as an adenoma with high grade dysplasia, ≥25% villous component or ≥10 mm diameter or CRC) was detected in 9% of individuals in this population. 1256/1276 individuals also performed a FIT and 1060/1276 collected a feces sample for a sDNA test [23].

For the molecular profile, data will be compared with the Dutch general population using existing data of sporadic CRC under the age of 70 years [24].

#### Sample size calculation

The main endpoint of the study is the diagnostic yield of advanced colorectal neoplasia among HL survivors detected by surveillance colonoscopy, which will be compared with the diagnostic yield performed in the general population [22].

Based on a 9% prevalence of advanced colorectal neoplasia in the asymptomatic general population, an increase to 15% of more in HL survivors after adjustment for age would be a significant change. To detect such a difference with 80% power, we need to include at least 259 study participants (based on the two-sided test for two independent proportions with 5% significance level). An interim analysis will be performed after the inclusion of 100 participants. At this point, when the detected prevalence of advanced colorectal neoplasia in the study population is 30% or higher, the difference between the two groups will be considered significant with a power of 80% and alpha level of 0.0006 (based on the group-sequential tests for two proportions).

#### Cost-effectiveness analyses

We will use the well-established microsimulation screening analysis (MISCAN) model to determine the cost-effectiveness of colonoscopy, FIT and sDNA test surveillance in HL survivors compared to FIT screening, e.g. the Dutch CRC screening program [25–28].

This MISCAN model will be performed to estimate the size of health benefits and costs of a surveillance program. In this mathematical model, a large number of fictitious individual life histories are simulated in each of which several colorectal lesions can emerge. The influence of the implementation of a surveillance program will be simulated, which can change some of the life histories.

This model will be able to estimate incidence, prevalence and mortality of CRC, and the results and effects of surveillance. The costs and the number of life-years gained for the population with and without the implementation of surveillance will be calculated.

The MISCAN model will be used to estimate the optimal time of initiation, interval and frequency of colonoscopies. These results will be used for the CRC surveillance recommendation in HL survivors.

### Study procedures

#### Colonoscopy

All patients will receive oral and standard written information about the preparation and the colonoscopy by their treating physician or by the gastroenterologist. The preparation will be performed as for routine colonoscopy by ingesting a commonly prescribed oral electrolyte lavage solution. Standard methods of conscious sedation (midazolam and/or fentanyl citrate or propofol) and cardiopulmonary monitoring will be used during the procedure. The colonoscopy will be performed by experienced gastroenterologists (>1000 colonoscopies and certified for performing colonoscopies in the Dutch population-based CRC screening program). Quality measures of colonoscopy will include registration of location of deepest insertion, withdrawal time, quality of preparation (Boston scale), colonoscopy difficulty (5-point scale), patient discomfort (Gloucester comfort scale) and level of sedation (Leeds score).

In the presence of colorectal neoplasia, polypectomy will be performed or biopsies will be taken according to standard protocol. The following data will be collected concerning colorectal neoplasia: number, morphology (Paris classification), size (measured with an open biopsy forceps), location (cecum, ascending, hepatic flexure, transverse, splenic flexure descending, sigmoid or rectum) and details about the polypectomy.

In the presence of a polyp of ≥10 mm, field biopsies will be taken and a fragment of the polyp will be allocated for study purposes after routine pathological evaluation. Four biopsies of normal mucosa of the transverse colon and two to four biopsies of normal mucosa of the descending colon will be taken (in both patients who did and who did not receive infradiaphragmatic irradiation). The transverse colon is the colonic segment that usually receives the highest dose of irradiation in infradiaphragmatic radiotherapy, whereas the descending colon receives a low dose of irradiation. In case of an additional surgical resection of a neoplastic lesion, part of the resection specimen will be allocated for study purposes. Study material will be stored at the participating hospitals and shipped to the Netherlands Cancer Institute for analyses.

